## Abstract

**Background:**

The SafeBoosC project aims to test the clinical value of non-invasive cerebral oximetry by near-infrared spectroscopy in newborn infants. The purpose is to establish whether cerebral oximetry can be used to save newborn infants’ lives and brains or not. Newborns contribute heavily to total childhood mortality and neonatal brain damage is the cause of a large part of handicaps such as cerebral palsy. The objective of the SafeBoosC-IIIv trial is to evaluate the benefits and harms of cerebral oximetry added to usual care versus usual care in mechanically ventilated newborns.

**Methods/design:**

SafeBoosC-IIIv is an investigator-initiated, multinational, randomised, pragmatic phase-III clinical trial. The inclusion criteria will be newborns with a gestational age more than 28 + 0 weeks, postnatal age less than 28 days, predicted to require mechanical ventilation for at least 24 h, and prior informed consent from the parents or deferred consent or absence of opt-out. The exclusion criteria will be no available cerebral oximeter, suspicion of or confirmed brain injury or disorder, or congenital heart disease likely to require surgery.

A total of 3000 participants will be randomised in 60 neonatal intensive care units from 16 countries, in a 1:1 allocation ratio to cerebral oximetry versus usual care. Participants in the cerebral oximetry group will undergo cerebral oximetry monitoring during mechanical ventilation in the neonatal intensive care unit for as long as deemed useful by the treating physician or until 28 days of life. The participants in the cerebral oximetry group will be treated according to the SafeBoosC treatment guideline. Participants in the usual care group will not receive cerebral oximetry and will receive usual care. We use two co-primary outcomes: (1) a composite of death from any cause or moderate to severe neurodevelopmental disability at 2 years of corrected age and (2) the non-verbal cognitive score of the Parent Report of Children’s Abilities-Revised (PARCA-R) at 2 years of corrected age.

**Discussion:**

There is need for a randomised clinical trial to evaluate cerebral oximetry added to usual care versus usual care in mechanically ventilated newborns.

**Trial registration:**

The protocol is registered at www.clinicaltrials.gov (NCT05907317; registered 18 June 2023).

**Supplementary Information:**

The online version contains supplementary material available at 10.1186/s13063-023-07699-x.

Thus, mechanically ventilated newborns are a high-risk population. Given the instability of the newborn’s pulmonary and circulatory physiology, it is possible that the addition of cerebral oxygenation monitoring by non-invasive near-infrared light technology (cerebral oximetry) plus a treatment guideline, as an addition to the complex treatment and extensive monitoring of these newborns, may increase their chance of surviving without neurodevelopmental impairment [8].

### The preceding SafeBoosC trials

The SafeBoosC-IIIv builds on the execution of the SafeBoosC-II [9] and the SafeBoosC-III trials [10]. The clinical context is that the risk of death as well as the risk of severe brain injury and neurodevelopmental impairment is high in extremely preterm infants and that the transition from intrauterine life constitutes specific risks of hypoxia due to the immature lungs, heart, and vasculature.

The SafeBoosC-II trial evaluated if treatment guided by cerebral oximetry could reduce the time when the brain was hypoxic (or hyperoxic) [9]. Cerebral oximetry by near-infrared spectroscopy was continued for the first three days of life in infants born before 28 weeks of gestational age. A total of 166 infants were randomised over 18 months, across eight European newborn intensive care units. The results showed that it was possible to reduce the time when the brain was hypoxic by more than 50%. Furthermore, there were fewer who died or suffered from severe brain injury in the intervention group, but more intervention group infants suffered from damage to the lungs and eyes. The trial was not powered for clinical outcomes, and indeed none of these differences were statistically significant. Therefore, the consortium was enlarged to conduct the SafeBoosC-III trial, a randomised, phase 3 trial at 70 sites in 17 countries [10]. A total of 1601 extremely preterm infants (gestational age < 28 weeks) were randomised within 6 h after birth, to receive treatment guided by cerebral oximetry for the first 72 h after birth versus usual care. The intervention effect of cerebral oximetry was neutral, as the relative risk for the primary outcome (death or severe brain injury at 36 weeks’ postmenstrual age) was 1.03, 95% confidence interval (CI) 0.90 to 1.18. 

The clinical context of the present SafeBoosC-IIIv trial is intensive care in less immature, although newborn infants. Basically, the brain of all patients that require intensive care is at risk of hypoxic-ischaemic injury, cerebral oximetry by near-infrared spectroscopy is a rational approach to timely detection, and intervention and a trial sequential analysis of 23 trials in children and adults has demonstrated a trend towards benefit, and more than 2300 participants are needed to reach a definitive answer [11]. The SafeBoosC-IIIv, added to the SafeBoosC-III trial, has the potential to do that.

The SafeBoosC consortium presently consists of neonatologists worldwide from over 60 neonatal intensive care units, working together to improve neuroprotective care for critically ill newborns. We here share our plans in the hope that other parties, who consider cerebral oximetry a promising add-on to the monitoring of patients during intensive care, may decide to test the benefits and harms in ways so that the results can be combined.

## Methods/design

### Objective

The objective of the SafeBoosC-IIIv randomised clinical trial is to evaluate the benefits and harms of cerebral oximetry added to usual care versus usual care in mechanically ventilated newborns. The hypothesis is that the intervention will decrease a composite outcome of death or moderate to severe neurodevelopmental disability and/or increase the mean PARCA-R non-verbal cognitive score at 2 years of corrected age.

### Trial design

The trial is an investigator-initiated, multinational, randomised, pragmatic phase III clinical trial. Sixty neonatal intensive care units across 16 countries will be randomising 3000 newborns in total. The trial protocol is in agreement with the SPIRIT guidelines (Table 1) (Additional file 1) [12].

**Table 1 Tab1:** Schedule for enrolment, intervention and assessment, based on the SPIRIT 2013 guidance for protocols of clinical trials. Asterisk symbol (*) indicates the following: if approved by the local ethics committee, deferred informed consent or prior informed assent may be sought. Time to ask parents for deferred consent will be decided individually by clinical staff members

Visit description	Consent and randomisation	Follow-up #1	Follow-up #2
Visit code	V0	V1	V2
Time period	0–6 h after mechanical ventilation has been initiated	28 days of life	2 years of corrected age
Assessing inclusion and exclusion criteria	X		
Informed consent (can be obtained before initiation of mechanical ventilation)*	X		
Allocation to experimental or control group	X		
Serious adverse reactions (SARs)		X	X
Serious adverse events (SAEs)		X	X
Explanatory variables		X	
Secondary outcomes		X	
Exploratory outcomes		X	X
Neurodevelopmental disability			X
All-cause mortality		X	X

### Inclusion criteria

The inclusion criteria are as follows: newborns with gestational age more than or equal to 28 + 0 weeks, postnatal age less than 28 days, predicted to require mechanical ventilation for at least 24 h (the primary analysis will be ‘as randomised’ thus including infants who are ventilated for shorter times), and signed prior informed parental consent or deferred parental informed consent or absence of opt-out.

### Exclusion criteria

The exclusion criteria are as follows: no available cerebral oximeter, suspicion of or confirmed brain injury, or congenital heart disease likely to require surgery.

### Participation in other trials

Participants may participate in other trials if such this does not interfere with the SafeBoosC-IIIv trial, for example by allowing clinical staff access to cerebral oxygenation values in the usual care group or exclude a treatment in the cerebral oximetry group that would be clearly indicated by the SafeBoosC treatment guideline to reduce cerebral hypoxia.

### Participant discontinuation and withdrawal

The participants’ parents are free to withdraw their infant from the intervention at any time and to decline the use of any future data. If the reason for discontinuation is given by the parents, it will be documented. The attending physician may, in case of safety concerns, withdraw a participant at any time. There are no pre-specified criteria for discontinuation of participants from the trial. Discontinuation of participants will not result in new participants as replacements.

### Recruitment

The feasibility of recruitment evaluating cerebral oximetry combined with the SafeBoosC treatment guideline was proven in the SafeBoosC-II trial [13] and recently in the SafeBoosC-III trial [14]. In the SafeBoosC-III trial, an average of 2.4 newborns were randomised per day (safeboosc.eu). Admission records indicate that the number of potential participants in SafeBoosC-IIIv is larger than for the SafeBoosC-III trial, and new countries and neonatal intensive care units are welcome to join.

### Randomisation

Participants will be randomised through central web-based randomisation. Block randomisation will be used with computer generated varying block sizes unknown to the investigators. Randomisation will be stratified by site, gestational age above or below 34 completed weeks, and expected surgery.

### Blinding

Clinical staff and parents cannot be blinded due to the nature of the intervention. Thus, the primary outcome will not be blinded in participants relying on parental reporting. If there is no contact with the parents, or if they do not return the questionnaire, data will be collected from health care records. All secondary outcomes will be assessed and reported at 28 days after birth by reviewing the newborn’s health care records. Investigators reviewing the health care records will, if possible, be blinded to the allocated intervention.

Data managers, the steering committee, statisticians, and writers of the two final abstracts (one assuming ‘A’ to be the experimental group and one assuming ‘B’ to be the experimental group) before unblinding of the groups will be blinded. The independent data safety monitoring committee will be provided statistics per allocation group named A and B but can request unblinding.

### Intervention

Participants randomised to the cerebral oximetry group will receive cerebral oximetry added to usual care, if possible before tracheal intubation or as soon as possible and within 6 h after mechanical ventilation has been initiated. Cerebral oximetry will continue during care in the neonatal intensive care unit, until the cardio-pulmonary function has been stabilised as indicated by the need for respiratory and circulatory support and evaluated by the responsible physician, until 28 days after birth, or until death. Cerebral oximetry will be used to modify clinical care to reduce cerebral hypoxia, according to the SafeBoosC treatment guideline. Being a pragmatic trial and given the costs and inconveniences of cerebral oximetry monitoring by near-infrared spectroscopy, the responsible clinicians will be free to use, or not use, cerebral oximetry during mechanical ventilation.

Participants randomised to the usual care group will receive usual care without access to cerebral oximetry monitoring.

### Treatment

All treatment options listed in the SafeBoosC treatment guideline are proposals for the responsible physicians on how to support the respiratory and cardiovascular system and keep cerebral oxygenation above the threshold as defined for each type of cerebral oximeter/sensor combination [6].

### Devices

If a given oximeter and sensor combination has been approved for clinical use in newborns and has been calibrated in the blood-lipid phantom [15], it may be used in the experimental group of the SafeBoosC-IIIv trial.

### Trial duration

Recruitment is expected to be completed within 36 months and the primary outcomes known for the last patient 2 years after.

### Outcomes

We will use two co-primary outcomes.

First is a dichotomous composite outcome of death from any cause or moderate-or-severe neurodevelopmental disability at 2 years of corrected age. Moderate-or-severe neurodevelopmental disability will be defined as one or more of the following: (1) cerebral palsy with Global Motor Function Classification System level 2 or higher; (2) the Parent Report of Children’s Abilities-Revised (PARCA-R) non-verbal cognitive function score below − 2 standard deviations (SD); (3) hearing loss corrected with aids or worse; or (4) vision impairment defined as moderately reduced vision of one eye, or only being able to perceive light or light reflecting objects, or blind in one eye with good vision in the contralateral eye. This relies on clinical routine data and the parents’ reports relying on their history with the child. The PARCA-R provides a high test–retest reliability and has been used in multiple clinical trials with 2-year follow-up [16].

Second is a continuous outcome comprising the non-verbal cognitive score of the Parent Report of Children’s Abilities-Revised (PARCA-R), a parental questionnaire, at 2 years of corrected age.

We will use two secondary outcomes.

First is days alive without mechanical ventilation within the first 28 days of life.

Second is one or more serious adverse events within the 28 first days of life. Serious adverse events are defined as one or more of the following: death from any cause, any brain injury diagnosed by imaging, seizures treated with antiepileptic medicine, necrotising enterocolitis defined as Bell’s grade 2 or more [17], sepsis defined as confirmed or suspected infection treated with antibiotics for 5 days or more, extracorporeal membrane oxygenation treatment, renal replacement therapy, use of vasopressor/inotropes, nitric oxygen treatment, and on mechanical ventilation at 28 days of life.

Exploratory outcomes will comprise cerebral palsy defined as Global Motor Function Classification System level 2 or above, at 2 years of corrected age; sensory deficit defined as any degree of vision or hearing impairment, at 2 years of corrected age; all-cause mortality at 2 years of corrected age; use of daily medication during the last 2 months, at 2 years of corrected age; the individual serious adverse events; and days alive without mechanical ventilation within the 28 first days of life. To minimise inter-variance regarding the clinical evaluation of cerebral palsy, vision impairment, and hearing impairment, we will, before initiation of the trial, develop a standard operation procedure with diagnostic criteria to be used by the outcome assessors.

### Statistical plan and data analysis

A fully detailed statistical analysis plan will be developed and published before enrolment is initiated. General principles are outlined below.  

The primary analysis of all outcomes will be based on the intention-to-treat population.

Mixed-effects linear regression and mixed-effects logistic regression will be used to analyse the continuous and dichotomous co-primary outcomes, respectively. In the regression models, we will adjust for the three stratification variables: ‘site’ will be included as a random effect, while ‘gestational age below or above 34 weeks of postmenstrual age’ and ‘group allocation’ will be included as fixed effects. Due to the relatively large sample size, we do not expect major unequal baseline characteristics in the two groups, and therefore, we do not a priori plan to include baseline variables as covariates in the statistical analyses. However, if baseline covariates will be unequal between the two groups, we plan to add sensitivity analyses adjusting for unequal baseline covariates to assess whether such baseline differences lead to different results. To correct for multiple testing, the threshold for statistical significance will undergo Bonferroni adjustment, and thus a *p*-value of 0.025 for each of the primary outcomes is chosen. The superiority of the intervention will only be claimed if at least one of the two co-primary outcomes is statistically significant. All other outcome results will be considered hypothesis-generating only.

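### The co-primary models promise adjustment for all three stratification variables but list the treatment term as the third and leave out expected surgery

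*Protocol article*

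**What the plan says.** Under Randomisation, the protocol article names three factors: "Randomisation will be stratified by site, gestational age above or below 34 completed weeks, and expected surgery".

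Under Statistical plan and data analysis, it specifies the models: "Mixed-effects linear regression and mixed-effects logistic regression will be used to analyse the continuous and dichotomous co-primary outcomes, respectively". It continues: "In the regression models, we will adjust for the three stratification variables". The terms that follow are:

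- site, which "will be included as a random effect";
- a term described as "gestational age below or above 34 weeks of postmenstrual age", and group allocation, which "will be included as fixed effects".

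The same paragraph adds: "we do not a priori plan to include baseline variables as covariates in the statistical analyses". Sensitivity analyses with further covariates are foreseen only if baseline characteristics turn out unequal. The significance threshold is a p-value "of 0.025 for each of the primary outcomes is chosen".

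**The concern.** The promise and the list cannot both be followed. An analyst who keeps to the promise fits expected surgery; one who keeps to the list does not. Each co-primary outcome therefore has two candidate primary models, and the choice should not be left until outcome data are available.

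The choice also affects the result. If expected surgery is prognostic and the randomisation balances it, a model without it attributes between-stratum variation to noise. The standard error is then larger than the real variability of the treatment comparison, so the test rejects less often than 2.5% under the null and gives up some power. In the logistic model the treatment odds ratio is also conditional on whichever covariates are included, so its meaning depends on whether surgery is in the model. The composite has only 73% stated power, so a free gain there is worth having.

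**Working it through.** **Step 1. Randomisation against model**

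| Randomisation factor | Term listed in the models |
|---|---|
| Site | Site, random effect |
| Gestational age, cut at 34 completed weeks | Gestational age, cut at 34 weeks, fixed effect |
| Expected surgery | None |
| (not a stratification factor) | Group allocation, fixed effect |

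Two of the three factors are covered. Expected surgery appears as a trial variable only under Randomisation. The imbalance-triggered sensitivity analyses would not normally bring it in, because stratification is there to prevent that imbalance.

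**Step 2. Reproduce the plan's power**

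- Composite (Sample size section): 20% v 16%, 1500 per group, two-sided alpha 2.5%, critical value z = 2.2414. Power = 72.9%; the plan says 73%. (A one-sided 2.5% test would give 81.4%, so the plan's figure is two-sided.)
- PARCA-R (Power of the continuous primary outcome): 1500 × 0.92 = 1380 survivors per group, SD 18, difference 3, alpha 2.5%. Power = 98.4%; the plan says more than 98%.

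Both calculations are unadjusted, so neither depends on the covariate list.

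**Step 3. Composite, with and without surgery**

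Assumptions not in the documents: 30% expected surgery, perfectly balanced; surgery odds ratio 2, 3 or 5; stratum risks set so that the group risks remain 20% and 16%. Normal approximation throughout.

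Let V_m = p(1 − p) at the pooled risk p = 0.18, so V_m = 0.18 × 0.82 = 0.1476. Let V_s = 0.7·p0(1 − p0) + 0.3·p1(1 − p1), with p0 and p1 the stratum risks that average to 0.18. A test that ignores the stratum uses V_m, while the comparison varies according to V_s. So:

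actual two-sided size = 2 × [1 − Φ(2.2414 × √(V_m / V_s))]

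| Surgery OR | p0, p1 | V_s | √(V_m/V_s) | Actual size |
|---|---|---|---|---|
| 2 | 0.147, 0.257 | 0.1451 | 1.009 | 2.4% |
| 3 | 0.127, 0.304 | 0.1410 | 1.023 | 2.2% |
| 5 | 0.102, 0.362 | 0.1334 | 1.052 | 1.8% |

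Power for the 4-point difference is Φ[(0.04 − 2.2414 × SE_test) / SE_true]. SE_true is the within-stratum standard error under the alternative. SE_test = √(2V_m/1500) without surgery; with surgery, V_m is replaced by the within-stratum variance.

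| Surgery OR | Power without surgery | Power with surgery | Gain (points) |
|---|---|---|---|
| 2 | 73.1% | 73.7% | 0.6 |
| 3 | 73.4% | 75.1% | 1.7 |
| 5 | 74.0% | 77.6% | 3.6 |

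**Step 4. PARCA-R, with and without surgery**

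Let R² be the share of variance explained by surgery (assumed 2, 5 or 10%). Omitting surgery inflates the standard error by 1/√(1 − R²). Actual size = 2 × [1 − Φ(2.2414/√(1 − R²))]. The true standard error is 18 × √(1 − R²) × √(2/1380).

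| R² | SE inflation | Actual size | Power without | Power with |
|---|---|---|---|---|
| 2% | 1.0% | 2.4% | 98.5% | 98.5% |
| 5% | 2.6% | 2.1% | 98.6% | 98.8% |
| 10% | 5.4% | 1.8% | 98.8% | 99.1% |

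The largest loss is about 0.3 points.

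**The case against.** The best defence is that this is a drafting slip. The principle, adjust for all three factors, is stated correctly; the section calls itself an outline of general principles; and a detailed analysis plan is promised before enrolment. The intention is indeed clear. But the article does not leave the covariates open: it lists them, and the list conflicts with both its own lead-in and the randomisation. That needs correcting wherever the model is finally written down.

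It is also fair to say that the effect is small and in the safe direction. A conservative test cannot manufacture a false claim of superiority. Without surgery in the model, the composite still has about its stated 73% power, so what is lost is an available gain. The 3.6-point figure needs an odds ratio of 5.

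Three stronger readings are tempting, and the documents do not support them.

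- *Infants would change age stratum.* Entry is allowed up to 28 days, so postmenstrual age at entry could pass 34 weeks in an infant born before then. That requires age to be re-measured at randomisation, which the text does not say. The variable is still called gestational age, and at birth the two ages coincide. This is a wording point only.
- *Material power is lost on both co-primary outcomes.* For PARCA-R the loss is negligible.
- *The Background proves that surgery is strongly prognostic.* The 0.5 SD deficit it cites compares surgical infants with the general population, not with other ventilated newborns, and the article itself calls it confounded. It makes a prognostic role plausible but does not size it. Taken at face value with 30% prevalence, it gives R² of about 0.3 × 0.7 × 0.5² = 5%, the middle row of the PARCA-R table.

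**Conclusion.** The inconsistency stands: as written, both co-primary models omit expected surgery, and the treatment term is counted as a stratification variable. The consequence is modest. There is no bias in the linear comparison. The tests are somewhat conservative: about 2.4 to 1.8% in place of 2.5% across the ranges examined, for both outcomes. The composite forgoes about 0.6 to 3.6 power points and PARCA-R at most about 0.3. These sizes rest on an assumed 30% prevalence (composite), assumed prognostic strengths, and perfect balance on surgery. If surgery is not prognostic, they vanish. No stated sample size or power figure needs to change. The reason to correct it is that the primary model must be unambiguous before outcomes are seen.

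**What to change.** Replace the covariate sentence with wording such as: all models include treatment allocation and are adjusted for the three stratification variables, namely site (random effect), gestational age below or above 34 completed weeks as used in the randomisation (fixed effect), and expected surgery, yes or no, as recorded at randomisation (fixed effect). As a minor point, drop the reference to postmenstrual age so that the age term carries the stratification definition.

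The analysis plan should carry the same list. The cost is a wording change and one extra model parameter. Expected surgery has to be known in order to randomise, so no new data are needed.

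### Expected balance is used as the reason to leave prognostic covariates out of the primary models, and observed inequality decides which ones enter a sensitivity analysis; gestational age (continuous) and postnatal age should be prespecified instead

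*Protocol article*

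**What the plan says.** The section Statistical plan and data analysis of the protocol article sets out mixed-effects logistic and linear models for the two co-primary outcomes. Site is a random effect. The fixed effects are the allocated group and "gestational age below or above 34 weeks of postmenstrual age".

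The reason for going no further is "Due to the relatively large sample size, we do not expect major unequal baseline characteristics in the two groups". From this the article concludes that "we do not a priori plan to include baseline variables as covariates in the statistical analyses". If covariates do prove unequal, "we plan to add sensitivity analyses adjusting for unequal baseline covariates to assess whether such baseline differences lead to different results". The section names no such covariate and gives no criterion for calling one unequal.

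Two candidate covariates must be known at entry because eligibility depends on them. Under Inclusion criteria the trial takes "newborns with gestational age more than or equal to" 28 + 0 weeks and "postnatal age less than 28 days". Postnatal age appears in neither primary model.

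**The concern.** The inference from expected balance to no adjustment rests on the wrong premise. Randomisation already protects against bias from baseline differences. In a randomised trial, covariates are adjusted for mainly because they explain variation in the outcome and so raise power, and they do this under perfect balance too. A large sample makes imbalance less likely but does not make a prognostic covariate less useful.

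The replacement rule has a related weakness. It selects variables by how far the arms happen to differ, which says nothing about whether they predict death, disability or the PARCA-R score. In the logistic model, adding a prognostic covariate moves the odds ratio even when that covariate is perfectly balanced. A gap between the primary and the triggered result would therefore not by itself show that imbalance mattered.

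What is at stake is some power on the composite, which has the thinner margin of the two co-primary outcomes, and a sensitivity analysis that would be hard to read.

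**Working it through.** **1. The plan's own figures.** The inputs are 20% versus 16%, 1500 per arm and alpha 2.5% (Sample size), and 8% deaths, SD 18 and a 3-point difference (Power of the continuous primary outcome). The article does not state sidedness. Two-sided testing, z = 2.241, reproduces its figures.

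- Composite: SE = √[(0.20·0.80 + 0.16·0.84)/1500] = 0.01401. Power = Φ(0.04/0.01401 − 2.241) = Φ(0.614) = 73.0%, or 72.9% with pooled variance. Stated: 73%.
- PARCA-R: 1500 × 0.92 = 1380 scored per arm. SE = 18·√(2/1380) = 0.685. Power = Φ(3/0.685 − 2.241) = 98.4%. Stated: more than 98%.
- With 20% loss to follow-up (Challenge 3): composite 62.1% (stated 62%), PARCA-R 95.3% (stated more than 95%).

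No stated figure is wrong.

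**2. Gain on the composite.** The documents give no R², so a range is assumed. Unadjusted and covariate-adjusted logistic regression were simulated with marginal risks of 20% and 16%, 1500 per arm, one standard normal covariate, no site effect and 4000 trials per setting. R² is the variance of the covariate-based risk in the control arm divided by 0.20 × 0.80.

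| Odds ratio per SD | R² | Power unadjusted | Power adjusted | Gain (points) |
|---|---|---|---|---|
| 1.00 | 0 | 72.2% | 72.0% | −0.2 |
| 1.22 | 0.006 | 72.8% | 72.9% | 0.1 |
| 1.49 | 0.025 | 74.6% | 75.5% | 0.9 |
| 1.82 | 0.05 | 73.1% | 75.8% | 2.7 |
| 2.23 | 0.09 | 72.8% | 77.0% | 4.2 |
| 2.72 | 0.13 | 73.4% | 79.5% | 6.1 |

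The unadjusted column varies by simulation error (SE about √(0.73·0.27/4000) = 0.7 points). Both analyses use the same simulated data, so the gain column is steadier. A useless covariate costs nothing material.

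**3. Gain on PARCA-R.** Here the residual SD is 18·√(1 − R²). Power goes from 98.4% to 98.8% (R² 0.05) or 99.1% (R² 0.10). With 20% loss it goes from 95.3% to 96.2% or 97.0%.

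**4. What the 34-week split already captures.** Assume gestational age is uniform over 28 to 41 weeks. The between-group variance of the split is (6/13)(7/13)·6.5² = 10.5 and the total is 13²/12 = 14.1, so the split holds about 75% of the linear variance. A triangular distribution (28 to 41.5 weeks, mode 34) gives about 66%. For the remainder alone to reach R² 0.05, gestational age would have to explain roughly 0.05/0.34 = 0.15 to 0.05/0.25 = 0.20 of outcome variance in total. Continuous gestational age by itself is therefore likely to sit towards the low end of the table. The contribution of postnatal age cannot be determined from the documents.

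**5. Effect on the odds ratio.** In the same simulations the marginal odds ratio of 0.76 became 0.74 conditionally at R² 0.09 and 0.73 at R² 0.13, with the covariate independent of the allocated group.

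**The case against.** The strongest reply is that this is a preference about efficiency and not an error. The article gives general principles and promises a detailed analysis plan, which may name covariates and define inequality. Its power figures all reproduce. The primary models are not bare, since they hold site and a gestational-age split. The benefit of the two proposed covariates is not shown anywhere in the documents. A linear gestational-age term may also fit poorly, because the Background describes different causes of respiratory failure in preterm and term infants.

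Most of this stands, and it limits the point. The absence of a covariate list or a threshold is not the complaint, because an analysis plan may supply both. What remains is the stated principle, which gives balance as the reason for omission and inequality as the route to inclusion. An analysis plan that follows it would inherit the faulty premise. The possible misfit is a reason to fix the functional form in advance, not to leave the variable out.

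A reader might infer that the data choose the model on which superiority is claimed. They do not: adjustment for unequal covariates is confined to sensitivity analyses. A reader might also infer that the trigger will fire often by chance. That would need a testing rule and a number of variables, and the article gives neither.

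The same section has a separate inconsistency. The article says "Randomisation will be stratified by site, gestational age above or below 34 completed weeks, and expected surgery", yet the model terms count the allocated group as the third stratification variable and omit expected surgery. That needs its own correction and does not answer this point.

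**Conclusion.** The point holds as a minor matter of analysis choice. Expected balance does not justify leaving out prognostic covariates, and observed inequality is a poor way to select them. The primary type I error is not affected.

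The gain is on the composite: 0 to 1 point of power for R² up to 0.025, about 3 points at 0.05 and about 6 at 0.13, from a base of about 73%. This rests on an assumed R² beyond the terms already modelled and on a simulation with one normal covariate and no site effect. The lower part of the range is the more plausible for gestational age. For PARCA-R the gain is under 1 point without loss to follow-up at R² up to 0.10.

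The documents do not support a claim of large savings in sample size, because they give no prognostic strength and the simple variance formula applies to the outcome that already has ample power. Nor is the change wholly free, given the conditional odds ratio and the need to settle the functional form.

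**What to change.** In both primary models, prespecify gestational age at birth as a continuous covariate, with its form fixed in advance and in addition to the stratification terms, and postnatal age at randomisation. Include both whatever balance is observed. Replace the imbalance-triggered analysis with one prespecified sensitivity analysis containing the stratification terms only. Delete the argument from expected balance.

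For the composite, report a standardised risk difference beside the odds ratio. The odds ratio is already conditional on site and the gestational-age split, and it would become conditional on the new covariates too.

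The cost is a few sentences in the analysis plan, settled before any unblinded data are seen. No extra infants are needed. No extra data should be needed either, since both variables must be known to establish eligibility; that they are recorded in usable form is an inference, because the article does not list the baseline data set.
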